### Statistical considerations

Given patient preference to avoid extracorporeal tubes as well as the other perceived advantages of ERC, we estimate that PTBD would have to be at least 20% more effective in achieving successful biliary drainage to change clinical practice. Assuming that PTBD will be 90% effective in achieving successful biliary decompression, we estimate that 160 patients (80 per study group) would provide a power of at least 85% to detect a 20% absolute difference between study groups on the basis of Fisher’s exact test, with a two-sided significance level of 0.05. To address potential losses to follow-up, the sample size is inflated by 15%. Thus, a total of 184 subjects will be enrolled.

For analysis of the primary endpoint, we will use a chi-square test to compare the proportion of patients achieving a 50% reduction from baseline in serum bilirubin level within 3 weeks in the PTBD and ERC groups using the intention-to-treat (ITT) principle. All randomized subjects will comprise the ITT population. A secondary analysis will explore the potential variability by study site and baseline serum bilirubin on the primary outcome measure. Center differences will be examined by including study site as a covariate in a mixed-effects logistic regression model. Since there will be roughly 25 centers with variable sample sizes, study site will be modeled as a random effect. In addition to the defined ITT analysis sample, a per-protocol sample will be defined as a subset of the ITT sample. This sample will be used for secondary sensitivity analyses of the primary and secondary outcomes. The per-protocol sample will include all randomized subjects that do not have the following protocol deviations: eligibility violation, non-adherence to the randomized treatment, or missing primary outcome. The secondary endpoints will be compared between treatment arms using a chi-square test or *t* test for independent means, as appropriate. There will be no adjustment for multiple comparisons in the pre-specified secondary analyses – including any patient-centered outcomes defined in the planning phase – but all additional exploratory analysis results will be interpreted more conservatively using a significance level of 0.01

Recognizing that the study population may be heterogeneous in ways which could differentially impact the success of ERC vs. PTC, we plan on performing pre-defined exploratory analyses of treatment differences in the primary outcome, adjusting for possible prognostic variables including: (1) age, (2) Body Mass Index (BMI), (3) Charlson Comorbidity Index, (4) presence of proven malignancy, (5) stricture of Bismuth type, (6) presence of significant unilateral lobar atrophy, and (7) recruitment at a center enrolling an average of at least four patients/year. Each covariate will be evaluated individually first in a logistic regression model that includes an interaction effect with the treatment. Interactions will be examined at significance level of 0.15, though the trial may be underpowered to assess such interactions. If significant interaction (statistical and clinical) is concluded, subgroup analyses may be considered. A multi-variable model that includes covariates that contributed significantly as treatment modifiers individually may then be constructed.

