### Follow-up

All follow-up decisions pertaining to the need for repeat procedures to address inadequate drainage or incomplete tissue sampling, or the decision to refer the patient for the alternative procedure will be dictated by treating physicians. All enrolled subjects will be followed for 6 months after the index (randomly assigned) procedure, primarily through review of their medical records.

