### Outcomes

The primary endpoint of successful biliary drainage will be defined as a 50% reduction in bilirubin level within 3 weeks of the study intervention without additional ERC or PTBD during that timeframe.

Secondary endpoints will include:An alternative definition of successful biliary drainage, defined as improvement in the serum bilirubin level to ≤ 2.5 mg/dL as a result of the index (randomization) intervention without the need for additional PTBD or ERC. This bilirubin level is considered informative because it is the threshold most commonly used by oncologists to administer chemotherapyAdverse events related to PTBD and ERC, defined according to standard consensus guideline documents published in the interventional radiology [5] and gastroenterology [7] literature, respectivelyMalignant tissue diagnosis, defined as a definitive diagnosis of malignancy documented in the subject’s medical record. We recognize that a fraction of patients will not have malignant obstruction, will not require a tissue diagnosis (known alternative primary cancer), or that a “gold standard” diagnostic test may not be available within the follow-up period in patients who are not diagnosed with cancer. We do, however, expect that patients with cancer in whom a tissue diagnosis is needed and possible will be allocated evenly between study groupsTotal number of procedures, hospitalizations, and cancer-specific treatments during the 6-month follow-up period

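### The per-protocol sample drops patients with a missing primary outcome even from the sensitivity analyses of adverse events and other secondary outcomes, where that exclusion has no purpose

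*Protocol article*

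**What the plan says.** Under Statistical considerations, the protocol article sets up two analysis samples. The first is intention-to-treat: "All randomized subjects will comprise the ITT population". The second is a per-protocol subset that excludes patients with any of three deviations: "eligibility violation, non-adherence to the randomized treatment, or missing primary outcome". On its use the article states: "This sample will be used for secondary sensitivity analyses of the primary and secondary outcomes". No secondary outcome is exempted.

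Under Outcomes, the primary endpoint is "a 50% reduction in bilirubin level within 3 weeks of the study intervention without additional ERC or PTBD during that timeframe". The secondary endpoints listed there include procedure-related adverse events, malignant tissue diagnosis, and counts of procedures, hospitalizations and cancer treatments. Under Follow-up, the data source is given: "All enrolled subjects will be followed for 6 months after the index (randomly assigned) procedure, primarily through review of their medical records".

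**The concern.** The first two exclusions describe departures from the plan: the patient should not have been enrolled, or did not receive the assigned procedure. The third is different. A missing bilirubin outcome is something observed, or not observed, after the procedure, and a complication can bring it about, for instance through early death or transfer elsewhere.

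For the primary outcome the exclusion at least has a plain reason, since a patient without the outcome cannot be classified. For an adverse event it has none, because the event can be in the record when the bilirubin result is not. A patient with a documented complication and no evaluable drainage outcome is therefore removed from the per-protocol safety comparison together with the complication.

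Safety carries weight in this trial. The Background hypothesizes that a drainage advantage of PTBD will be offset partly by the safety of ERC. A sensitivity analysis of adverse events should show whether the main safety result is robust, and this one can move the result through its own exclusion rule.

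**Working it through.** **The plan's own figures.** The planning text reads: "Assuming that PTBD will be 90% effective in achieving successful biliary decompression", and "160 patients (80 per study group) would provide a power of at least 85% to detect a 20% absolute difference between study groups", by "Fisher’s exact test, with a two-sided significance level of 0.05". Exact enumeration at 80 per arm, 90% against 70%, gives power of 86.7%, so the statement reproduces. The inflated total also reproduces: 160 × 1.15 = 184, or 92 per arm. The margin is 184 − 160 = 24 patients, and 24/184 = 13.0%. None of these figures depends on the per-protocol definition.

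**What the rule does.** The article gives no adverse-event rate, no death rate and no missingness by arm, so its effect can only be illustrated. For one arm let

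- a = true adverse-event rate,
- m = probability that the primary outcome is missing, given an adverse event,
- q = probability that it is missing, given no adverse event.

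Considering only the missing-outcome exclusion, the per-protocol event rate is

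a(1 − m) / [a(1 − m) + (1 − a)(1 − q)].

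If m = q this equals a, and there is no bias. If m > q it is below a, so the rate is understated.

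**Illustration.** All inputs are assumptions, with q = 5% in both arms. The building blocks are:

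- a = 30%, m = 25%: 0.225 / (0.225 + 0.665) = 25.3%
- a = 30%, m = 50%: 0.150 / (0.150 + 0.665) = 18.4%
- a = 20%, m = 25%: 0.150 / (0.150 + 0.760) = 16.5%
- a = 20%, m = 50%: 0.100 / (0.100 + 0.760) = 11.6%

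| True rate, PTBD / ERC | m, PTBD / ERC | Per-protocol rate, PTBD / ERC | True difference | Per-protocol difference |
|---|---|---|---|---|
| 30% / 20% | 25% / 25% | 25.3% / 16.5% | +10 | +8.8 |
| 30% / 20% | 50% / 25% | 18.4% / 16.5% | +10 | +1.9 |
| 30% / 20% | 25% / 50% | 25.3% / 11.6% | +10 | +13.7 |
| 30% / 30% | 25% / 25% | 25.3% / 25.3% | 0 | 0 |
| 30% / 30% | 50% / 25% | 18.4% / 25.3% | 0 | −6.9 |

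Differences are PTBD minus ERC, in percentage points.

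**Are the scenarios extreme?** The expected number excluded per arm is 92 × [a·m + (1 − a)·q]. In the second row this is 92 × 0.185 = 17.0 plus 92 × 0.090 = 8.3, or 25.3 in all. In the last row it is 17.0 + 10.1 = 27.1. Both are slightly above the plan's margin of 24, so these rows lie toward the severe end. The first row loses 10.1 + 8.3 = 18.4.

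**Reading the table.** Every per-protocol rate is too low, because m exceeds q throughout. The difference is badly distorted only where m differs between arms, and then it can shrink, grow or change from zero. Nothing in the article says which case will apply.

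**The case against.** The strongest reply is that very few patients may be affected. The endpoint is a fall within 3 weeks, not a measurement at 3 weeks. A patient who had already reached the 50% fall, or who needed another ERC or PTBD in the window, may have a known outcome. A patient who dies early without reaching the fall can reasonably be counted as a non-success. On that reading the patient is not missing and stays in the sample. This stands: a patient who dies or leaves early is dropped only if the outcome is treated as missing, and the article does not say that it will be.

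The second reply is that this is a supplementary analysis. The intention-to-treat population keeps everyone, so any events lost from the per-protocol set remain visible beside it. This also stands. The article names intention-to-treat explicitly only for the primary endpoint, but nothing confines the main secondary comparisons to the per-protocol sample.

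The third reply is that every rate in the illustration is assumed, and that the 24-patient margin is an allowance for sizing, not a forecast of outcomes missing because of complications. That is correct, and it limits what can be said about size.

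None of these replies gives the exclusion a purpose for outcomes that do not depend on the bilirubin result. Nor is the rule a detail left to another document: the article states it, and states that it covers secondary outcomes.

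**Conclusion.** The point holds as a flaw in one stated rule for a supplementary analysis. The per-protocol sample for adverse events, tissue diagnosis, procedures and hospitalizations is selected on a post-procedure variable that is irrelevant to measuring them and that a complication can influence. Event rates are understated if missingness is higher after an event; the difference between arms is distorted as well if that missingness differs by arm. In the illustration, a true difference of 10 points is shown as anything from 1.9 to 13.7. These figures rest wholly on assumed rates, and the document fixes neither size nor direction.

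A reader might infer more: that patients who die early disappear from the trial's safety comparison, or that the per-protocol result must flatter the procedure with more complications. The document supports neither. The all-randomized comparison is not affected by this rule, early death may be classed as non-success, and the distortion can go either way.

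**What to change.** Apply the missing-primary-outcome exclusion only to the per-protocol analysis of the primary outcome. For adverse events and the other secondary outcomes, define the per-protocol sample by eligibility and adherence to the randomized treatment alone.

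This takes one or two sentences, needs no new data, and changes neither the sample size nor the power. The cost is that the per-protocol sets differ slightly between endpoints, so each table should show its own denominators.

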## Discussion

The INTERCPT trial will be the only randomized comparison of PTBD vs. ERC as the initial intervention for patients with suspected malignant hilar obstruction. This is a fundamental question in clinical practice that has remained unanswered because of the practical and methodological complexities of such a trial.

To maximize practicality and generalizability, we have adopted a pragmatic study design that includes only one protocol-driven intervention – randomization to PTBD or ERC. All other clinical decisions are deferred to treating physicians as clinically appropriate. We believe that this experimental question is particularly suited for such a pragmatically designed trial because the varying approaches to managing this highly complex disease process between patients and across practice settings constrains protocol standardization and threatens the generalizability of a more traditional randomized controlled trial (RCT) design. Standardizing procedural approach, re-interventions, and medication administration, for example, would not only be impossible to ensure, but would also critically limit external validity because of the tremendous complexity in decision-making and the extreme variability in approaches between providers and institutions.

We appreciate that physicians may select ERC vs. PTBD based on stricture characteristics and other considerations such as the patient’s overall health and goals of care. However, in many practice settings, ERC is typically attempted first because of its perceived advantages. Moreover, stricture characteristics are often unknown beforehand because routine MRI/ magnetic resonance cholangiopancreatography (MRCP) has not been obtained. Fundamentally, the goal of our study is to determine, at the point of care, whether ERC or PTBD is preferable as the initial treatment of patients with suspected MHO, even though stricture characteristics, resectability status, and a definitive diagnosis may not be known – the exact scenario often faced in real-world clinical practice. Furthermore, this study may determine whether a strategy of routine “planning” MRI/MRCP in these cases to guide procedural selection improves clinical outcomes.

We recognize that patients with suspected MHO are often initially managed by gastroenterologists who may be biased in favor of ERC and may prematurely re-divert patients assigned to the PTBD group back to ERC, reducing the likelihood of successful drainage via PTBD. However, this potential bias will be mitigated by the fact that suspected MHO patients are generally managed in multi-disciplinary fashion by a Tumor Board, minimizing the influence of any single provider on the care of a patient. We also recognize that ERC is well established in the United States and Europe as the initial management option for MHO, and thus it is possible that the results of this study would not impact clinic practice. However, we have selected a large enough effect size such that a demonstrated superiority of PTBD would have to be strongly considered in clinical decision-making and guidelines.

The INTERCPT trial will be the first to determine whether PTBD or ERC is the better initial intervention for a patient with suspected MHO, or whether the treatment approach should be individualized based on stricture characteristics or other factors.

### Trial status

This RCT began enrolling patients in October of 2017.

## Abbreviations

CT: Computed tomography
ERC: Endoscopic retrograde cholangiography
INTERCPT: INTerventional Radiology vs. ERC for Perihilar Tumors
MHO: Malignant biliary obstruction
MRCP: Magnetic resonance cholangiopancreatography
MRI: Magnetic resonance imaging
PTBD: Percutaneous transhepatic biliary drainage
